#### SF-36

Assessment of musculoskeletal disease consists of two parts: the expected outcome of a particular treatment and the effect of a particular treatment on the function, QoL and satisfaction of participants. The combination of general instruments and specific questionnaires may be the best way to evaluate the surgical outcomes, since misinterpretations and conclusions with limited reliability can be efficiently avoided [45]. In this study, the specific AKSS questionnaire and the generic instrument of the SF-36 will be utilized.

The SF-36 consists of eight scaled scores covering 36 items: vitality, physical functioning, bodily pain, general health perceptions, physical role functioning, emotional role functioning, social role functioning and mental health. Each scale independently produces the score from 0 to 100 and the lower score indicates a worse disability.

### The additional outcomes

Both physical factors and psychological factors contribute to dissatisfaction [46]. Hence, the patient satisfaction rate or expectation rate will be used to control the psychological factors. Participants will be asked to rank their satisfaction with a 5-point scale (1 = very unsatisfactory; 2 = unsatisfactory; 3 = neutral; 4 = satisfactory; 5 = very satisfactory), and the frequency of the “very satisfactory” determines the satisfactory ratio [47]. Patient’s expectation rating is ranked with 3-point scale (1 = positive; 2 = neutral; 3 = negative). The incidence of side effects of analgesia (nausea/vomiting/dizziness/sleepiness) and the TEAS (local irritation, redness, contact dermatitis, or muscle ache) will be recorded daily.

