#### TEAS interventions

TEAS will be performed using XCH-C1 equipment (ShangHai Nuo Cheng Co.). Based on the theory of Traditional Chinese Medicine, two circular electrodes (2 cm × 2 cm) will be placed around the surgical knee acupoints of SP9 (YINLINGQUAN) and GB34 (YANGLINGQUAN). SP9 is located at the hollow between the inferior edge of the medial tibial condyle and the medial edge of the tibia. GB34 is located at the lateral side of the calf in the hollow, anterior and inferior to the fibular head [31]. Before electrode attachment, E will shave and sterilize the skin with 75% ethyl alcohol. The TEAS produces a balanced, asymmetrical biphasic waveform with a pulse width of 200 μs, and a strong but comfortable current amplitude [32]. Intervention duration will be set as 30 min per day for 2 weeks [33]. Participants will be required not to change the current settings by themselves during the application of TEAS. A 30-min TEAS will be daily applied prior to a 30-min rehabilitation (including flexibility, strength, range of motion, balance and gait exercises [34]).

For the active TEAS (5 Hz/100 Hz/mixed) group, a continuous frequency of 5 Hz/100 Hz/mixed will be used. The placebo group will deliver a strong but comfortable current for 30 s which then gradually vanishes over the next 15 s. One study [35] has demonstrated that this new sham device can promote the effect of blinding through eliminating expectation bias and clarifying the true efficacy of TEAS. In this way, a sound emitted at the end of TEAS will indicate the endpoint of the TEAS treatment, which achieves the best blinding effect on participants and the outcomes assessor. Meanwhile, the participant will be told that: the TEAS works all the time during its application and they may or may not experience sensations from the TEAS unit due to different sensation thresholds of different people.

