### Outcomes evaluations

Pain intensity (rest and movement) and the American Knee Society Score (AKSS) are the primary outcomes. Secondary outcomes include active range of motion (AROM) of the knee that was operated on, surface electromyography of both quadriceps, the modified 30-s sit to stand test, additional use of analgesics and the 36-item Short Form health survey (SF-36). The additional outcomes include patient satisfaction rate, patient expectation rate and the incidence of analgesia-related side effects.

The pain intensity, AROM, incidences of analgesia-related and TEAS-related side effects will be daily recorded. Evaluation of the patient satisfaction rate and patient expectation rate will be conducted after the first episode of the TEAS intervention. The SF-36 will be evaluated at two time points: before the TEAS intervention, and 2 weeks after the TEAS intervention. The assessment time points of the remaining outcomes are before the surgery, after the surgery before the TEAS intervention(at POD 3), and 1 week and 2 weeks after the TEAS intervention.

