### Statistical analysis

All data will be analyzed using the statistical package for IBM SPSS Statistics V21. The intention-to-treat (ITT) and per-protocol sets (PP) will be analyzed. Continuous data are presented as mean ± standard deviation (SD), and categorical variables are described as percentages. Baseline data will be collected and analyzed. Continuous data with normal distribution and homogeneity variance will be analyzed using analysis of variance (ANOVA). Otherwise, the Kruskal-Wallis *H* test will be performed.

Statistical analysis includes the following four aspects. Firstly, the repeated measurement data will be analyzed using the mixed-effects model or generalized estimating equation (GEE) or generalized linear mixed models (GLMMs). Secondly, the correlation between different outcomes will be analyzed using the multiple linear regression or logistic regression. In this study, NRS, sEMG or AROM are independent variables, whereas the AKSS or m30STS test are dependent variables. Psychological factors serve as covariance. Thirdly, the safety analysis of TEAS will be compared between groups using *χ*^2^ test or Fisher’s exact test. Fourthly, health economic evaluation (cost-effectiveness analysis) will be performed. A *P* value < 0.05 (two-side) is considered statistically significant.

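### Satisfaction is scheduled after the first TEAS session, so as an outcome it cannot compare the two-week regimens

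*Protocol article*

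**What the plan says.** All places are in the protocol article.

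- **Status.** Outcomes evaluations: "The additional outcomes include patient satisfaction rate, patient expectation rate and the incidence of analgesia-related side effects". The Abstract gives the same list.
- **Timing.** Outcomes evaluations: "Evaluation of the patient satisfaction rate and patient expectation rate will be conducted after the first episode of the TEAS intervention". Pain, AROM and side effects are recorded daily, and SF-36 has two time points of its own. The section then says "The assessment time points of the remaining outcomes are before the surgery, after the surgery before the TEAS intervention(at POD 3), and 1 week and"; the list ends with an assessment at week 2. Satisfaction already has its own time point, so it is not one of these remaining outcomes.
- **Course.** TEAS interventions: "Intervention duration will be set as 30 min per day for 2 weeks".
- **Item and summary.** The additional outcomes: "Participants will be asked to rank their satisfaction with a 5-point scale", and "the frequency of the “very satisfactory” determines the satisfactory ratio". A literature reference supports the rule; no reason is given.
- **Second role.** The additional outcomes: "the patient satisfaction rate or expectation rate will be used to control the psychological factors". Statistical analysis: "Psychological factors serve as covariance".

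**The concern.** The trial compares four regimens, each given daily for two weeks. An outcome of those regimens has to be measured once they have been delivered, or at least once they differ. A rating after session 1 describes one session on POD 3.

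This bears hardest on G3, the arm the trial's hypothesis concerns. Its distinguishing feature is the day-to-day change of frequency, and on day 1 no change has yet taken place. A difference or a null result between G3 and the single-frequency arms at that point says nothing about mixing. Read at face value, the published satisfaction rates would be taken as patients' verdict on two weeks of treatment.

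The summary rule adds a smaller concern. A patient who answers level 4, labelled satisfactory, falls outside the satisfactory ratio, and levels 1 to 4 are pooled. If that ratio became the only basis for comparing arms, information already collected would go unused.

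**Working it through.** **Timing: the passages side by side**

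1. TEAS starts at POD 3 (Randomisation and allocation concealment) and runs daily for 2 weeks, which is 2 × 7 = 14 sessions. The rating follows session 1 of 14.
2. The Abstract describes G3 as alternating daily 5 Hz and 100 Hz TEAS. The Discussion confirms that the two frequencies are applied separately on alternate days. After session 1, a G3 patient has had either 5 Hz (as in G1) or 100 Hz (as in G2).
3. Pulse width, session length and the rule for setting amplitude are the same in all active arms, and the Discussion names frequency as the only factor that varies. At the time of rating, G3 therefore differs from G1 or G2 in nothing that has been delivered.
4. The Discussion describes the low-frequency effect as delayed but lasting, and says that alternating frequencies may delay tolerance. Both are features of a course, and one session cannot show them.

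**Summary rule: how much information the top-level split keeps**

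The article gives no satisfaction rates, so there is no stated figure to reproduce. Its sample size concerns pain and is used here only for the number per group: 2 × (1.96 + 0.84)² × 2.88² / 2² = 32.55, rounded up to 33; 33 / 0.85 = 38.8, rounded up to 39; 4 × 39 = 156, as stated.

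Under proportional odds with level probabilities p1 to p5, the information is proportional to 1 − Σp³. With t = p5, the split of level 5 against levels 1–4 keeps 1 − [t³ + (1 − t)³] = 3t(1 − t). Efficiency near no effect is the ratio 3t(1 − t) / (1 − Σp³).

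For power I took 33 per group, an assumed odds ratio of 3 and two-sided α = 0.05. Ordinal power is Φ(ln 3 × √V − 1.96), with V = (33/6)(1 − Σm³) and m the mean of the two arms' level probabilities. Split power is that of the usual two-proportion test.

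| Assumed placebo distribution, levels 1–5 | 3t(1 − t) | 1 − Σp³ | Efficiency | Loss | Power, ordinal vs split |
|---|---|---|---|---|---|
| .05 .10 .30 .45 .10 | 0.270 | 0.880 | 0.31 | 69% | 67% vs 36% |
| .05 .10 .25 .40 .20 | 0.480 | 0.911 | 0.53 | 47% | 69% vs 52% |
| .03 .07 .20 .35 .35 | 0.683 | 0.906 | 0.75 | 25% | 66% vs 59% |
| .02 .05 .13 .30 .50 | 0.750 | 0.846 | 0.89 | 11% | 60% vs 56% |
| .01 .02 .07 .20 .70 | 0.630 | 0.649 | 0.97 | 3% | 45% vs 41% |

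Among these distributions, the loss exceeds half only when 10% choose the top level. It is slight when half or more do.

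**The case against.** **The early rating may be intended.** The article also uses satisfaction or expectation to control for psychological factors, and an early rating paired with expectation suits that role better than a late one. This stands as an explanation of the timing. It does not make the rating an outcome of the course, and the Abstract and Outcomes evaluations both list it as an outcome.

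**A later rating may exist.** The schedule figure (Fig. 2) is not shown. A reader might infer that satisfaction is certainly asked only once. The text says nothing of a second rating, but the figure could show one, and the two would then need reconciling.

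**The cut-off is legitimate.** This largely stands. Reporting the top category is a permissible convention, and the article cites support for it. Three stronger readings are tempting, and the document supports none of them:

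- *Most of the scale's information is thrown away.* All five levels are recorded. Even if only the split were analysed, most of the information would be lost only when few patients choose the top level.
- *Satisfied patients are classed as dissatisfied.* The article defines one ratio and attaches no such label to the remaining levels.
- *The planned between-arm test loses precision.* Statistical analysis names no between-arm test of satisfaction. It says only that categorical variables are described as percentages.

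**The size is assumed.** This also stands. The figures depend on assumed distributions and on proportional odds. If arms differed mainly between levels 4 and 5, the split would not be at this disadvantage.

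**Conclusion.** The timing point holds on the article's text. Satisfaction is listed as an outcome of a two-week daily course but is scheduled after session 1, when G3 has received a single frequency. As planned, it cannot compare the regimens. This rests on the plain reading of Outcomes evaluations and on G3 alternating by day, and it is subject to what Fig. 2 shows.

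The cut-off is not an error. It is a reason to analyse the full scale that is being collected anyway. The gain is unknown in advance, and the range of about 3% to 69% of the information is illustrative.

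The importance is minor. This is an additional outcome, and neither the primary outcomes nor the sample size depends on it.

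**What to change.** 1. Keep the rating after session 1 if it is wanted as a psychological measure, and describe it as such.
2. Ask the same 5-point item again at the end of week 2 and name that rating as the satisfaction outcome. Ask it before the active/placebo guess, which is due within 5 minutes of the last TEAS, so that the guess cannot colour the answer.
3. If Fig. 2 already shows a later rating, bring Outcomes evaluations into line with it and state which rating is the outcome.
4. Compare arms on all five levels with a rank-based or ordinal (for example proportional-odds) method, and report the top-level percentage descriptively.

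**Cost.** One extra question per participant, some care over its order at the last session, and an odds ratio or rank measure that is slightly harder to read than a percentage. No change to the number of participants is needed.

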### Statistical analysis

All data will be analyzed using the statistical package for IBM SPSS Statistics V21. The intention-to-treat (ITT) and per-protocol sets (PP) will be analyzed. Continuous data are presented as mean ± standard deviation (SD), and categorical variables are described as percentages. Baseline data will be collected and analyzed. Continuous data with normal distribution and homogeneity variance will be analyzed using analysis of variance (ANOVA). Otherwise, the Kruskal-Wallis *H* test will be performed.

Statistical analysis includes the following four aspects. Firstly, the repeated measurement data will be analyzed using the mixed-effects model or generalized estimating equation (GEE) or generalized linear mixed models (GLMMs). Secondly, the correlation between different outcomes will be analyzed using the multiple linear regression or logistic regression. In this study, NRS, sEMG or AROM are independent variables, whereas the AKSS or m30STS test are dependent variables. Psychological factors serve as covariance. Thirdly, the safety analysis of TEAS will be compared between groups using *χ*^2^ test or Fisher’s exact test. Fourthly, health economic evaluation (cost-effectiveness analysis) will be performed. A *P* value < 0.05 (two-side) is considered statistically significant.

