**Methods/design:**

This is a double-blind, randomized controlled trial. A total of 156 patients are randomly assigned to: G1, 5 Hz TEAS; G2, 100 Hz TEAS; G3, mixed TEAS (alternative use of daily 5 Hz and 100 Hz TEAS) and G4, placebo TEAS. In the G1, G2 and G3 groups, TEAS is conducted at acupoints SP9 and GB34 of the leg that was operated on (at a wave of continuous, balanced and asymmetrical biphasic square, with a pulse width of 200 μs, and a strong but comfortable current) for 30 min prior to a 30-min rehabilitation session per day for 2 weeks. In G4 group, TEAS is delivered at a strong but comfortable current for 30 s, then the current is gradually decreased to none over the next 15 s. The primary outcomes are measured before surgery, at baseline (POD 3, before TEAS intervention), week 1 and 2 after TEAS intervention with the Numeric Pain Rating Scale and The American Knee Society Score. The secondary outcomes include: (1) Active range of motion of the knee that was operated on; (2) Surface electromyography of both quadriceps; (3) Modified 30-s sit to stand test; (4) Additional usage of analgesia; and (5) SF-36. The additional outcomes include: (1) Patients’ satisfaction rate; (2) Patient’s expectation rate; and (3) Incidence of analgesia-related side effects. To test the blinding of participants and assessors, they are asked to guess whether the subjects received active or placebo TEAS within 5 min after the latest intervention. The safety and financial cost of TEAS are assessed.

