### Sample size

The sample size will be calculated using pain ratings from the previous studies [27–29]. The formula:$$ n=\frac{2{\left({Z}_{\alpha }+{Z}_{1-\beta}\right)}^2{\sigma}^2}{\Delta ^2} $$

An effect size (△) of 2 with a standard deviation (SD) of 2.88 between low-frequency (LF) TEAS and placebo-TEAS (*n* = 33 × 4/0.85 = 156), an △ of 2.35 with a SD of 2.56 between high-frequency (HF) TEAS and placebo-TEAS (*n* = 19 × 4/0.85 = 95), an △ of 1.1 with a SD of 0.7 between mixed TEAS and placebo-TEAS (*n* = 7 × 4/0.85 = 35) [26]. Using this information, a four-group study will be established: 33 patients in each group, α = 0.05 (two-sided), β = 0.2 (80% power) [30]. Considering a possible sample loss of 15%, the final sample size will be set with 39 patients in each group.

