### Randomisation and allocation concealment

Participants who meet the screening criteria will be randomized into four balanced groups: G1, G2, G3 and G4. The randomization sequence will be computer-generated by an independent research staff (C) with a 1:1:1:1 ratio using SPSS 21.0.

At POD 3 and before the TEAS application, three physical therapists (D, E, F) will be mainly responsible for the treatment sessions and outcomes evaluation. Initially, D will perform the basic measurements of participants in four groups and double-check whether the sensation in the leg that was operated on is normal. After D leaves the ward, E will apply a 30-min TEAS intervention and subsequently F will perform a 30-min rehabilitation session per day in four groups. One TEAS intervention and one rehabilitation constitute one treatment session. Immediately after the end of one treatment session, D will return to the ward, evaluate and record the outcomes according to the trial design. Researchers except for C and E will be blinded to the treatment allocation. Randomisation and allocation concealment in a light-tight sealed envelope until E firstly reveals the TEAS intervention according to the random number sequence at POD 3. Participants will be required not to communicate with any other researchers, participants and care providers to minimize the risk of potential bias. After the latest TEAS intervention, participants and outcome assessors will be asked to guess whether the subjects received active TEAS or placebo TEAS within 5 min to evaluate the blinding quality.

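### No stated treatment comparison of NRS or AKSS adjusts for the POD 3 value, and the repeated-measures model is left open enough to pool pre-treatment with post-treatment visits

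*Protocol article*

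**What the plan says.** - **Longitudinal data** (Statistical analysis, first of four listed aspects): "the repeated measurement data will be analyzed using the mixed-effects model or generalized estimating equation (GEE) or generalized linear mixed models (GLMMs"). No fixed effects, baseline term, contrast or time point follows.
- **Continuous data** (same section, preceding paragraph): "Continuous data with normal distribution and homogeneity variance will be analyzed using analysis of variance (ANOVA"), with Kruskal-Wallis otherwise. These sentences come directly after the one saying that baseline data will be collected and analysed.
- **Covariates** (same section): the only ones named are psychological factors, and they belong to the regressions that relate one outcome to another, not to the comparison of arms.
- **Visits** (Abstract, Methods/design): "The primary outcomes are measured before surgery, at baseline (POD 3, before TEAS intervention), week 1 and 2 after TEAS intervention". Two of these four occasions precede any TEAS.
- **Daily pain** (Outcomes evaluations): "The pain intensity, AROM, incidences of analgesia-related and TEAS-related side effects will be daily recorded". AKSS is among the outcomes left on the four-visit schedule.
- **Planning values** (Sample size): "An effect size (△) of 2 with a standard deviation (SD) of 2.88 between low-frequency (LF) TEAS and placebo-TEAS", and "33 patients in each group, α = 0.05 (two-sided), β = 0.2 (80% power").

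**The concern.** A pre-treatment value of the outcome is usually its best single predictor, and here it is collected for every participant on the day TEAS starts. The section names a covariate for a different purpose but does not use this one for the comparison of arms. Precision that costs nothing extra to obtain is therefore not secured by the plan.

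The second issue is which occasions count as responses. Under randomisation the expected difference between arms is zero before surgery and at POD 3. If those occasions enter as responses beside weeks 1 and 2, a group term averaged over visits mixes occasions with no possible treatment effect and occasions with one. The plan does not say that this term will be read, but nothing in it rules this out.

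**Working it through.** **Inputs from the article.** Δ = 2 and SD = 2.88 (low-frequency TEAS against placebo), two-sided α = 0.05, 80% power, 33 evaluable per arm, 15% loss; two pre-treatment and two post-treatment visits; pain recorded daily over two weeks of treatment.

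**Assumptions, not in the article.** Correlation ρ between any two occasions of 0.3 to 0.6 (0.7 where shown), equal SD at all occasions, and Δ constant after treatment starts. About 14 daily pain values are taken from two weeks of daily recording.

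**1. Reproduce the stated size.** n = 2(1.960 + 0.842)² × 2.88² / 2² = 32.6, so 33 per arm. Then 33/0.85 = 38.8, so 39 per arm and 4 × 39 = 156. This agrees with the article and uses no baseline correlation. Power at 33 per arm is 80.5% by the normal approximation and 79% by the t-test.

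**2. Adjust for POD 3 at one post-treatment visit.** Residual SD = 2.88 × √(1 − ρ²); equivalent unadjusted n = 33/(1 − ρ²). For comparison, a change-from-POD 3 contrast has SD 2.88 × √(2(1 − ρ)). Powers are from the t-test.

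| ρ | Residual SD | Power, adjusted | Equivalent n per arm | Power, change from POD 3 |
|---|---|---|---|---|
| 0 (unadjusted) | 2.88 | 79% | 33 | – |
| 0.3 | 2.75 | 83% | 36 | 65% |
| 0.4 | 2.64 | 86% | 39 | 72% |
| 0.5 | 2.49 | 89% | 44 | 79% |
| 0.6 | 2.30 | 93% | 52 | 87% |

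Adjustment beats both the unadjusted comparison and the change score at every ρ shown.

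**3. Group main effect, if one were read over all occasions.** Expected effect = Δ × (post-treatment occasions / all occasions). Variance of a participant's mean over k occasions = SD² × (1 + (k − 1)ρ)/k.

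- Four-visit schedule (AKSS): the effect is Δ × 2/4, half its size. The article gives no Δ or SD for AKSS. With the pain values as a stand-in for its standardised effect, 2.0 becomes 1.0, and t-test power is 52%, 42% and 38% at ρ = 0.3, 0.5 and 0.6.
- Daily NRS (2 pre-treatment, about 14 post-treatment): the effect is 2 × 14/16 = 1.75, a dilution of one eighth. Power by the normal approximation is 99%, 92% and 83% at ρ = 0.3, 0.5 and 0.7.

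**4. Like-for-like check when baselines stay in the model as responses.** For the mean of the two post-treatment visits (normal approximation, ρ = 0.3 / 0.5 / 0.7):

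- unadjusted: 94% / 90% / 86%
- contrast of post-treatment mean minus pre-treatment mean: 92% / 98% / >99%
- post-treatment mean adjusted for the pre-treatment mean: 98% / 99% / >99%

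**The case against.** The strongest reply is that this reads a choice into silence. The article does not say whether POD 3 is a response, a covariate or a constrained baseline, and fixed effects are commonly left to an SAP or a full protocol, neither of which is shown. That stands: this is an improvement to write in, not an error shown on the page.

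A second reply is that a longitudinal model with group-by-time terms already uses the baseline. In part it does. Step 4 shows that the before–after contrast reaches 92% to over 99%. Those figures average two visits, however, and must not be set against the single-visit figures in step 2. At one visit an unconstrained contrast with POD 3 is the change score, which does no better than the unadjusted comparison until ρ reaches 0.5. Constraining the arm means to be equal at POD 3 does recover essentially the precision of adjustment, but the article does not state that constraint.

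Three stronger readings are tempting, and the document supports none of them:

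- That POD 3 is planned purely as one more response. The article does not say so.
- That the trial will be judged on a diluted group main effect with power near 40–50%. No such test is specified. For pain, which is recorded daily, the halving would not apply if all days were modelled.
- That a failed normality check moves the repeated NRS and AKSS data to Kruskal-Wallis. The position of those sentences suggests that they may concern the baseline table only.

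**Conclusion.** The point holds as one of efficiency and clarity. No stated comparison of arms on NRS or AKSS adjusts for POD 3, and the model description allows pre-treatment and post-treatment occasions to be pooled. Randomisation protects against bias either way, and the figures of 33, 39 and 156 are correct without adjustment, so neither validity nor planned size is in question.

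The gain is from 79% to about 83–93% single-visit power at 33 per arm, equivalent to 36–52 participants per arm. It depends on the assumed correlations of 0.3–0.6 and on the planning Δ and SD. The dilution (one half for AKSS, about one eighth for daily NRS) is conditional on a main-effect test that the article does not name.

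**What to change.** For NRS and AKSS, state one primary model:

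- a mixed model on post-treatment measurements only, with group, visit, group×visit, POD 3 value and POD 3×visit as fixed effects; or, to the same effect, keep POD 3 as a response with the arm means constrained equal at that visit;
- arm differences with 95% CI reported at one named visit;
- a statement of whether ANOVA and Kruskal-Wallis are meant for baseline data or for outcomes. If for outcomes, keep Kruskal-Wallis as a sensitivity analysis, since it uses neither baseline nor visit and gives no difference in points.

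This is a change of wording in the analysis plan, best made before unblinding. The data are already scheduled for collection, and the statistical cost is a few degrees of freedom.

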#### The American Knee Society Score (AKSS)

The AKSS is commonly used for outcomes evaluation after the TKA globally [39], including knee assessment (0–100) and functional assessment (0–100), a total of 200 points [40]. The knee assessment consist of three components: pain (0–50), range of motion (0–25) and stability (0–25). Deduction is determined by the presence and severity of flexion contracture (0–15), extension lag (EL, 0–15) and malalignment (0–20). Function is evaluated via walking (0–50) and climbing stairs (0–50) with deductions for walking aid (0–20). For each part, a negative score is possible and should be transformed to zero.

The knee stability evaluation consists of two parts: the anterior-posterior stability test and the lateral stability test. The procedure of the anterior-posterior stability test is the same as that of the anterior drawer test of the knee. During the lateral stability test, the surgical knee is flexed by 30°. The participant will be required to stand when measuring the lower extremity alignment, and the acute angle between two lines (anterior superior iliac spine to the midpoint of the knee, the midpoint of the knee to the midpoint of the ankle) will be recorded. Valgus of 5–10° is considered to be the normal alignment and three scores are deducted for each degree of malalignment outside this range [41]. For measuring EL, a towel roll will be placed under the heel of the knee that was operated on. The participant will be required to extend their knee as much as possible, and keep the knee as straight as possible to raise the lower extremity off the towel roll. The physical therapist keeps the goniometer in alignment to measure the degrees from the straight position. The number of degrees is subtracted from the knee extension AROM to obtain the degrees of EL [42].

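### The planned regressions of AKSS on NRS pain and AROM share content with their own outcome, so their coefficients cannot be read as evidence about function

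*Protocol article*

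**What the plan says.** The second of the four analyses in the Statistical analysis section is described thus: "the correlation between different outcomes will be analyzed using the multiple linear regression or logistic regression". The roles are then fixed: "NRS, sEMG or AROM are independent variables, whereas the AKSS or m30STS test are dependent variables". Psychological factors enter as covariates.

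The section on the American Knee Society Score describes the instrument as "including knee assessment (0–100) and functional assessment (0–100), a total of 200 points". The knee assessment has three positive components ("pain (0–50), range of motion (0–25) and stability (0–25"), with deductions for flexion contracture and extension lag (up to 15 points each) and malalignment (up to 20). On extension lag the section adds: "The number of degrees is subtracted from the knee extension AROM to obtain the degrees of EL". The functional assessment covers walking and stairs, 50 points each, with a deduction of up to 20 for walking aids.

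No passage limits the AKSS in the regression to its functional part, and none removes the pain or motion items first.

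**The concern.** Two of the three named predictors measure things that are scored inside one of the two named outcomes. NRS rates pain in the operated knee, and AKSS gives up to 50 points for pain. AROM measures motion of the same knee, AKSS gives up to 25 points for motion, and one of its deductions is computed from AROM. This is part-whole coupling: some association arises because the same content stands on both sides of the equation.

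What is at stake is interpretation. The Discussion hypothesises that mixed-frequency TEAS improves pain, muscle performance and knee function. A significant coefficient of NRS on AKSS would naturally be taken as support for the link from less pain to better function. It could appear even if walking, stair climbing and stability had no relation to pain. Adjusting for psychological factors does not remove shared items.

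**Working it through.** **1. The plan's own figure.** Knee: 50 + 25 + 25 = 100. Function: 50 + 50 = 100. Total: 200, as the protocol article states.

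**2. Shared points.** Pain plus motion is 50 + 25 = 75. That is 75/100 = 75% of the knee assessment and 75/200 = 37.5% of the total. Extension lag (up to 15 points) is derived from AROM. Flexion contracture (up to 15) is also a quantity of extension range.

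**3. Association induced by the overlap alone.** The document gives no AKSS SDs and no correlation between NRS and the AKSS pain item, so the following are assumptions:
- SDs: AKSS pain 10 to 15, motion 3, stability 3, function 15 to 25.
- Correlation of NRS with the AKSS pain item, and of AROM with the AKSS motion item: 0.7 to 0.9 in absolute size.
- Components independent of each other, deductions given no variance, and function and stability unrelated to pain or motion.
- n = 33 × 4 = 132, the number left after the 15% loss allowed for in the Sample size section.

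For total AKSS, induced r = r(item) × SD(item) / √(SD_pain² + 3² + 3² + SD_func²). For the knee part, drop SD_func². Values are absolute, since NRS and AKSS run in opposite directions. The test is t = r√130 / √(1 − r²). At n = 132, |r| must exceed 0.171 for two-sided P < 0.05.

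| Pairing | Smallest r | Largest r | P at the expected r |
|---|---|---|---|
| NRS, total | 0.7 × 10/√(100 + 18 + 625) = 0.257 | 0.9 × 15/√(225 + 18 + 225) = 0.624 | at most 0.003 |
| NRS, knee part | 0.7 × 10/√118 = 0.64 | 0.9 × 15/√243 = 0.87 | far below 0.001 |
| AROM, total | 0.7 × 3/√(225 + 18 + 625) = 0.07 | 0.9 × 3/√(100 + 18 + 225) = 0.15 | 0.095 to 0.42 |
| AROM, knee part | 0.7 × 3/√243 = 0.13 | 0.9 × 3/√118 = 0.25 | 0.004 to 0.12 |

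With NRS also in the model, the partial correlation of AROM with total AKSS is 0.08 to 0.17 (P 0.057 to 0.39).

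**4. Sensitivity.** These P values are taken at the expected correlation. In the weakest NRS case (r = 0.257) the power from overlap alone is about 85% (Fisher z). With a correlation of 0.5 to the AKSS pain item, pain SD 10 and function SD 25, r = 5/√743 = 0.18, P = 0.035 and power is about 56%. With 0.4, P = 0.093. For the knee part, power stays above 99% in both cases.

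A different assumption, SDs proportional to item ranges, gives a joint built-in R² = (r_p² × Var_pain + r_r² × Var_motion) / Var(AKSS), where r_p and r_r are the correlations of NRS and AROM with their AKSS items. For (r_p, r_r) from (0.5, 0.7) to (0.9, 0.95), R² is 0.25 to 0.69 for the knee part and 0.11 to 0.30 for the total. By chance, two predictors would give about 2/131 = 0.015. Halving the pain and motion SDs lowers the total-score range to 0.04 to 0.10. The AROM share is sensitive too: with proportional SDs its own correlation with the total is √(0.49 × 625/8750) = 0.19 to √(0.9025 × 625/8750) = 0.25.

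**The case against.** The other side has several fair points.

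- The protocol article calls this analysis a correlation between outcomes. It plans no mediation analysis and does not itself say that the regression will show that analgesia improves function. The randomised arms and the repeated-measures models answer the trial's hypothesis. This stands, and it limits the point to a supportive analysis.
- m30STS is already a dependent variable and sEMG already a predictor, and neither shares an AKSS component. This stands too.
- The article does not say which AKSS score enters the regression, and an analysis plan that is not shown could name the functional part. That is possible, but the text as written names AKSS, which it defines as the 200-point score, and carries no restriction.
- All the magnitudes rest on assumed SDs and correlations. This is true. The shared points are fixed by the document, but the size of the induced association is not.

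A reader might go further and infer that both pain and AROM are almost certain to reach P < 0.05. The figures do not support this for AROM and the total score, and for NRS they depend on the assumed correlation. A reader might also infer that any association with AKSS is largely built in. That description suits the knee assessment (75% of points), but not the total (37.5%, with an NRS R² of 0.07 to 0.39 on the main assumptions). Nor does the coefficient say nothing about function: it blends overlap with whatever real relation exists and cannot separate them.

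**Conclusion.** The point holds in a confined form. In the NRS-AKSS and AROM-AKSS regressions the outcome contains its predictors' content, and nothing in the document removes it. The coefficients therefore cannot be taken as evidence that less pain or more motion goes with better function.

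For NRS, overlap alone is enough for significance at the expected correlation under the main assumptions. It becomes borderline for the total score if NRS correlates 0.5 or less with the AKSS pain item. For AROM and the total score, the main assumptions give no significant induced association, before any coupling through the contracture and extension-lag deductions. That result depends on the small motion SD assumed, so the documents do not settle its size.

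It would be wrong to infer that the randomised comparisons of NRS or AKSS are biased: the overlap does not enter them. The change is worth making, but it does not touch the primary comparison, the sample size or the safety analysis.

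**What to change.** In the Statistical analysis section, state that for regressions on NRS or AROM the AKSS dependent variable is the functional assessment (walking and stairs, less the walking-aid deduction), with m30STS kept as planned. If the knee assessment is to be modelled, first remove its pain, range-of-motion, flexion-contracture and extension-lag items.

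This costs one sentence, best written before the data are analysed. The sub-scores are already recorded, so no extra measurement, visit or patient is needed. The small downside is that the full AKSS is no longer modelled as one score in this supportive analysis.
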